### Nutritional assessment

The nutritional assessment includes anthropometric measurements, body composition by BIA, handgrip strength (HGS) by a handgrip dynamometer, 7-point subjective global assessment (7p-SGA) and the dietary intake by 24-h food recall.

The BMI is calculated by dividing weight (kg) by the square of the height (m^2^). BMI (kg/m^2^) is classified according to the cutoffs proposed by the Pan American Health Organization criteria for the elderly [11] as underweight (BMI < 23 kg/m^2^), normal body weight (BMI ≥ 23 and < 28 kg/m^2^), overweight (BMI ≥ 28 and < 30 kg/m^2^), and obese (BMI ≥ 30 kg/m^2^). BMI is being also classified according to the conventional Worth Health Organization as underweight (BMI < 18.5 kg/m^2^), normal body weight (BMI ≥ 18.5 and < 25 kg/m^2^), overweight (BMI > 25 and < 30 kg/m^2^), and obese (BMI ≥ 30 kg/m^2^). Anthropometric parameters are assessed with patients in the standing position and by the same observer. The following measurements are evaluated in the right side of the body using either a non-stretchable tape or a skinfold caliper (Cescorf® Scientific model, Cescorf Equipaments, Brazil) as appropriate: calf circumference (CF), right mid-upper arm circumference (MUAC) and triceps, biceps, triceps, subscapular and suprailiac skinfold thickness. An average of 3 consecutive measurements are considered for each site assessed. The body fat percentage is calculated as proposed by Durnin & Wormersley [12].

The HGS evaluates strength and muscle quality [13], using a handgrip dynamometer (E-clear®, model EH 101, Cei Technology, Taoyuan City, Taiwan). With the arms along the body, the patients are encouraged to press the tool with maximum strength in response to a voice command, as recommended by the American Society of Hand Therapists. The maximum contraction of the dominant arm for 3 s is evaluated. The measurements are repeated 3 times, and the highest value is considered and expressed in kg (and as percentage of controls with same age and sex).

The Subjective Global Assessment (SGA) [14], a well-validated tool to assess nutritional status, is being applied to all participants, in a version of 7 points, according to the CANUSA study [15]. The 7p-SGA involves the assessment of medical history: changes of body weight and dietary intake, gastrointestinal symptoms, and functional capacity. In addition, a physical examination of body fat reserves, muscle mass and presence of edema is also evaluated. Each component has a score from 1 to 7. The 7p-SGA scale [16], validated to Portuguese [17] classifies patients as well-nourished (score 7 to 6), mild to moderate protein-energy wasting (score 5 to 3) and severe protein-energy wasting (score 2 to 1) [16].

Phase angle, intra- and extracellular water, total body water, fat mass, fat free mass, and skeletal muscle mass are measured by the single multifrequency BIA device InBody™ S10 (Biospace Co., Ltd., Korea) with the software from the equipment. The patient is placed in the supine position, with arms and legs separated from the body. Any metal object is removed. Eight electrodes are positioned, two in each limb, according to manufacturer instructions.

In total, the nutritional assessment lasts about 30 min in each patient in addition to the 7p-SGA, which lasts for another 10 min.

The dietary intake of all patients is assessed through a 24-h dietary recall interview (R24h). The R24h consists of defining and quantifying all foods and beverages ingested in the pre-interview period, which may be in the preceding 24 h or, more commonly, in the day previous to the assessment [18]. Quantitative assessment of intake is being done using DietBox nutritional calculation software and diet quality is assessed using the Diet Quality Index, as previously described [19].

Sarcopenia is being evaluated by the SARC-F, a self-reported questionnaire [20]. This tool has 5 components related to functional status: strength, assistance with walking, rising from a chair, climbing stairs, and falls. Each component scores from 0 to 2, with higher scores suggesting sarcopenia.

### Charlson comorbidity index (CCI)

The Charlson comorbidity index [21] is a widely used method predicting mortality by weighting comorbidities, validated in the renal disease context [22]. The CCI contains 19 issues including diabetes, hemiplegia, renal disease, congestive heart failure peripheral vascular disease, chronic pulmonary disease, mild and severe liver disease, leukaemia, lymphoma, metastatic tumor, and acquired immunodeficiency syndrome, each of which was weighted according to their potential influence on mortality.

### Non-invasive hemodynamic monitoring

Non-invasive hemodynamic monitoring is evaluated using the Finometer® device (Finapress Medical System B.V., Amsterdam, The Netherlands) [23], which is a low-risk device able to measure beat-to-beat continuous blood pressure [24]. All patient’s measurements is being taken in the supine position, after a rest period of 10 min. The Finometer is calibrated for at least 2 min as recommended by the manufacturer [23]. All measurements are conducted in a quiet room, between 7 and 10 am. Blood pressure is measured in the nondominant arm and recorded for 7 min. The finger cuff is placed on the middle finger. The following parameters are evaluated: systolic, diastolic and mean blood pressure, systolic volume, heart rate, stroke volume, cardiac output, and total systemic peripheral resistance. Active data will be exported with the BeatScope Easy software (MedTech Inc., Burlington, Ontario, Canada), according to the BeatScope 5-s averages method.

### Pittsburgh sleep quality index (PSQI)

The PSQI is an instrument used to measure the quality and patterns of sleep in adults [25], validated to the Portuguese Language [26]. Seven domains are evaluated: subjective sleep quality, sleep latency, sleep duration, sleep efficiency, sleep disturbances, use of sleep medication, and daytime dysfunction over the last month. Patients are classified as poor sleepers or good sleepers when the sum of scores is > or < 5, respectively.

### Subjective sleepiness

The Epworth Sleepiness Scale (ESS) assesses subjective daytime sleepiness, which is a self-administered questionnaire [27], validated to the Portuguese Language [28]. Scores rate on a scale of 0 to 3 how likely they are to fall asleep in 8 common situations. Higher scores indicate more sleepiness.

### Laboratory biomarkers

About 8–10 mL of blood specimens are collected in two different tubes (serum and plasma) at the baseline visit and saved in a box with ice. Specimens are centrifuged, identified and stored in the biorepository at the temperature of − 80° Celsius, in the Investigation Laboratory 16 (LIM-16) of the *Universidade de Sao Paulo*, Sao Paulo, Brazil. Biomarkers of bone and mineral metabolism such as FGF-23 and Klotho will be measured at the end of the study period.

Standard laboratory measurements such as urea, creatinine, estimated glomerular filtration rate (eGFR), hemoglobin, calcium, phosphate, bicarbonate, serum albumin, 25(OH) vitamin D and parathyroid hormone (PTH) will be collected from the patient’s charts.

### Power analysis

The sample calculation to obtain *p* < 0.05, with a cross-sectional design, and 80% of beta error, was calculated to require 197 individuals or 119 events. Based on the average monthly attendance of patients with the inclusion profile in the study and considering refusal and loss of follow-up in up to 20% of the sample, we plan to include this sample in 4.5–5 years.

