**Methods:**

AGNES is a prospective observational cohort that aim to investigate clinical, biochemical and demographic factors associated with RRT initiation and mortality of patients with CKD stage 4 or 5 who are aged 70 years and older. We plan to include 200 patients over 5 years. Clinically stable outpatients on conservative management for at least 6 months will be recruited from the Nephrogeriatric Clinic at the *Hospital das Clinicas da Universidade de Sao Paulo*, Brazil. Eligible patients are submitted to a full clinical examination, geriatric assessment, and blood test at baseline. Following the baseline visit the patients are being monitored during an observational follow up period of at least 12 months during which patients will be contacted in the clinic at their regular follow up or by phone until either RRT initiation or death occurs. This cohort includes evaluation of cognition by the education-adjusted 10-point Cognitive Screener (10-CS), frailty by Fried index score, a complete nutritional assessment (by body composition assessment, global subjective assessment and dietary intake), comorbidities by Charlson comorbidity index and biochemical markers including FGF-23 and Klotho.

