## Methods

### Primary hypotheses

Our primary hypothesis is that mortality is associated with greater number of comorbidities and with a high impact of geriatric issues. The decision of beginning RRT will be more likely to occur in patients with fewer burdens of geriatric syndromes.

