### General study design

AGNES was designed as a prospective unblinded cohort from a single academic center, evaluating risk factors of mortality and biomarkers associated with beginning of RRT. Patients who agree to participate are signing the written informed consent. Baseline data are collected in the same day.

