### Statistical analysis

First, we will perform a descriptive analysis of the demographic, nutritional and clinical parameters of the included patients. Specific data includes geriatric syndromes, full nutritional assessments, muscle strength (based on HGS), body composition, sleep questionnaires, CCI, and non-invasive hemodynamic parameters. Continuous data will be presented as mean ± SD and categorical data will be presented as proportion. Normality distribution will be tested by D’Agostino omnibus test. Patients will be classified according to clinical evaluation according to the cognitive deficit, frailty, nutrition status, stage of renal function (4 or 5) and the presence of sleepiness and poor quality of sleep. Exploratory analyses will include an association between any of the above-mentioned clinical diagnoses with the 2 outcomes: death or beginning of renal replacement therapy. These outcomes will be closely monitored by the study team in the routine visits or and/or by telephone contact. A *p* value < 0.05 will be considered significant. Analyses will be performed using SPSS 22.0 (SPSS Inc., Chicago, IL, USA) and *GraphPad Prism® software* (GraphPad Software, Inc., CA, USA).

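### The power statement is misstated (80% beta, cross-sectional design), and its single count of 119 events is not tied to either of the two primary outcomes

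*Protocol article*

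**What the plan says.** The protocol article's only power statement is one sentence in Power analysis: the sample size was obtained "with a cross-sectional design, and 80% of beta error, was calculated to require 197 individuals or 119 events". No outcome, effect size or exposure share is attached to it. The same section allows for refusal and loss of up to 20%, but only in explaining how long recruitment will take.

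The surrounding text describes a different kind of study:

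- General study design: "AGNES was designed as a prospective unblinded cohort from a single academic center".
- Abstract, Methods: "We plan to include 200 patients over 5 years". Patients are observed for at least 12 months and contacted until RRT starts or the patient dies, whichever is first.
- Follow up: telephone calls every 4 months check both vital status and RRT. This section does not say that contact stops when RRT begins.
- Primary hypotheses: mortality is expected to rise with comorbidity and geriatric burden, and "The decision of beginning RRT will be more likely to occur in patients with fewer burdens of geriatric syndromes".
- Statistical analysis: associations are examined with "the 2 outcomes: death or beginning of renal replacement therapy", and a p "value < 0.05 will be considered significant".

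**The concern.** Two statements are wrong on their face. Beta is the type II error, so "80% of beta error" claims one chance in five of detecting the target effect. And "with a cross-sectional design" contradicts the cohort design. A cross-sectional study accrues no events over time, so the phrase also conflicts with the event count in its own sentence.

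The third difficulty is that one event count stands behind two primary hypotheses without saying which it serves. Under first-event follow-up, deaths and RRT starts draw on the same 200 patients, so every event of one kind removes a patient who could have supplied the other. A combined count of death or RRT would power neither hypothesis separately, and the effects predicted for geriatric burden would pull against each other within it.

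At stake is how a null result is read. With the slip silently corrected to 80% power, a reader could take the study as adequately powered for both outcomes when the text supports that for neither one specifically.

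**Working it through.** **Inputs from the protocol article.** 197 individuals or 119 events (Power analysis); 200 patients planned (abstract); alpha 0.05, sidedness not stated (Statistical analysis); refusal and loss up to 20% (Power analysis). Two-sided alpha is assumed below.

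**Reproducing 197 or 119.** This is not possible: no effect size, exposure share, event rate or test is given. The calculation can only be run backwards with Schoenfeld's formula, HR = exp[(z_alpha + z_power) / sqrt(D·a·(1−a))], where D is the number of events and a the exposed share (assumed).

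**What the beta slip does.** With D = 119 and a = 0.5:

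- Power 80%: z sum = 1.960 + 0.842 = 2.802; HR = exp(2.802/√29.75) = 1.67.
- Power 20%, as printed: z sum = 1.960 − 0.842 = 1.118; HR = exp(1.118/√29.75) = 1.23.

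Neither hazard ratio is in the document. The gap shows that the slip changes what 119 events would mean.

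**Share of patients who must have an event.** 119/197 = 60.4%; 119/200 = 59.5%; if the full 20% were lost, 119/160 = 74.4%. So 119 is attainable in principle for one outcome or for the two combined.

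**Both outcomes, first event only (abstract).** 2 × 119 = 238 > 200. If one outcome supplies 119, the other has at most 200 − 119 = 81. Power with D events for the effect that 119 detect with 80% is Φ(2.802·√(D/119) − 1.960):

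- D = 81: Φ(2.311 − 1.960) = 0.64.
- D = 100 (an even split with every patient having an event): 0.73.
- D = 80 (an even split of 160): 0.63.

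**Both outcomes, deaths after RRT counted.** Patients who must have both events: at least 238 − 200 = 38 of 200, 238 − 197 = 41 of 197, or 238 − 160 = 78 of 160. This is demanding but not impossible.

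**Illustrative event counts (hazards assumed, not in the documents).** Take an equal constant hazard h per year for each outcome, uniform accrual over 5 years, 1 further year of follow-up and no loss. With t = 2h, the first-event share is 1 − [exp(−t) − exp(−6t)]/(5t).

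| h per outcome | First events of 200 | Per outcome |
|---|---|---|
| 0.10 | 96 | 48 |
| 0.15 | 123 | 62 |
| 0.20 | 142 | 71 |
| 0.30 | 165 | 83 |

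With equal hazards the count per outcome stays below 119 throughout this range. The combined count passes 119 from h = 0.15 upwards. With 62 events the power formula gives 0.52.

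**Detectable HR at 80% power, two-sided, by exposed share (assumed).**

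| Events | 50% | 40% | 30% | 20% |
|---|---|---|---|---|
| 119 | 1.67 | 1.69 | 1.75 | 1.90 |
| 81 | 1.86 | 1.89 | 1.97 | 2.18 |
| 62 | 2.04 | 2.07 | 2.17 | 2.43 |

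**The case against.** A reader might infer that the study is arithmetically impossible, because 119 events cannot be reached for both outcomes with 200 patients. The document does not support that. The power sentence never requires 119 events per outcome. The limit of one event per patient rests on one phrase in the abstract; the Follow up section sets no stop at RRT, and the Discussion asks who is at higher risk of death when dialysis is started, which needs deaths after RRT. A combined endpoint could also reach the count: at an assumed 0.15 per year for each outcome, about 123 first events occur before any loss (about 99 if the full 20% were lost). All of this stands, and it makes the 238-patient result conditional.

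It can also be said that an article may leave the effect size to the full protocol, that the outcome associations are labelled exploratory in Statistical analysis, that the Discussion lists the number of patients among the limitations, and that hazards and exposure shares assumed here should not be written into the plan as fact. The first is fair, and the absence of an effect size is not itself the point. The last is also right: the assumed figures only show scale. The exploratory label does not settle the matter, because mortality and RRT start appear under Primary hypotheses.

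None of this rescues the two misstatements. The article chose to print the calculation, and it printed the error rate and the design wrongly.

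**Conclusion.** The power statement is wrong as written on two counts that need no assumption: the printed beta means 20% power, and the stated design contradicts the cohort and the event count. That the authors meant 80% power is an inference, though a safe one.

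The event count is also badly fixed, since it is not linked to death, to RRT or to their combination. The consequence depends on a rule that the article leaves unclear. If follow-up stops at the first event, at most one of the two primary outcomes can have 119 events, and the other is left with 81 or fewer and about 64% power at best for the same effect. If deaths after RRT count, 119 of each remains possible but needs at least 38 of 200 patients with both events. The 64% assumes two-sided alpha 0.05, the same exposure split for both outcomes, and an event in every patient. The figures based on hazards and exposure shares are illustrations only.

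**What to change.** Keep N = 200 and rewrite the Power analysis paragraph:

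1. State 80% power (20% beta) and the sidedness of alpha, and replace the cross-sectional basis with a time-to-event one.
2. Say whether the 119 events are deaths, RRT starts or the two combined.
3. Say whether deaths after RRT count, and bring the abstract and the Follow up section into line on this.
4. For death and for RRT separately, give the detectable hazard ratio over a range of event counts and exposure shares, using the sponsor's own expected event rates and the loss of up to 20%. For illustration, at an assumed 40% exposed: about 1.7 with 119 events, 1.9 with 81 and 2.1 with 62.

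The cost is one reworded paragraph, one reconciled follow-up rule and no extra patients. The downside is a less favourable stated detectable effect for at least one outcome.

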### Follow up

After a baseline visit, patients will be followed by telephone contact every 4 months to check mortality and the beginning of RRT. The follow up will last at least 12 months. In addition, patients will be routinely followed in the same outpatient clinic with an average interval between visits of 4 to 5 months. Patients can withdraw their consent to participate in the study at any time.

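### The up-to-20% allowance for refusal and loss enters only the recruitment time: 200 included patients cover 1.5% loss against the stated need for 197 individuals or 119 events

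*Protocol article*

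**What the plan says.** The Power analysis section of the protocol article gives the requirement in one sentence: the sample "was calculated to require 197 individuals or 119 events". The stated settings are "The sample calculation to obtain *p* < 0.05, with a cross-sectional design, and 80% of beta error". No effect size, exposure prevalence or event rate is given.

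The next sentence is the only place where attrition appears. It pools two things and leads to a statement about duration: "considering refusal and loss of follow-up in up to 20% of the sample, we plan to include this sample" in 4.5–5 years.

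The Methods paragraph of the Abstract sets the target: "We plan to include 200 patients over 5 years". The Follow up section says "The follow up will last at least 12 months", with telephone contact every 4 months, and lets patients withdraw consent at any time. Under Study visit procedures, a patient is included only after agreeing and signing the consent form.

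**The concern.** Refusal and loss to follow-up act at different points. Refusal happens before inclusion: it slows recruitment, and a longer recruitment period is the right answer to it. Loss happens after inclusion, and taking longer to include the same number of patients does not make up for it. It needs either a larger target or a lower stated power.

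The article names both in one allowance, applies the allowance to recruitment time only, and sets a target 3 patients above the requirement. The stated requirement, the expected attrition and the target do not fit together unless almost none of the 20% is loss.

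The power claim is what is at stake. The study examines many exposures against two outcomes, and its own Discussion lists the limited cohort size as a limitation. A reader of a non-significant association needs to know what power the cohort really had.

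**Working it through.** **Inputs from the article.** Required: 197 individuals or 119 events. Refusal plus loss: up to 20%, not split. Planned inclusion: 200. Significance level: 0.05.

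**Assumptions.** The level is two-sided, since sidedness is not stated. The phrase "80% of beta error" means 80% power. The calculation is event-driven, although the article calls it cross-sectional.

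**1. The plan's own figure.** 197 and 119 cannot be reproduced, because no effect size, exposure share or event rate is given. Under the assumptions above and an equal exposure split (a further assumption), the Schoenfeld formula 4 × (1.96 + 0.84)² / (ln HR)² returns 119 events at a hazard ratio of about 1.67. That hazard ratio is back-solved and is not a figure of the plan. The steps below do not need it.

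**2. Margin in the target.** 200 − 197 = 3, and 3/200 = 1.5%. Any loss after inclusion above 1.5% leaves fewer than 197 patients.

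**3. Implied event share.** 119/197 = 60.4%.

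**4. Patients, events and power by loss after inclusion (d).**

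- Patients retained = 200 × (1 − d).
- Events = patients retained × 119/197, if lost patients contribute none.
- Power = Φ(2.80 × √(events/119) − 1.96), which scales the assumed 80% power at 119 events. No hazard ratio or exposure share enters.
- Inclusion needed to retain 197 = 197/(1 − d), rounded up.

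| Loss after inclusion | Patients retained | Events | Power | Inclusion needed to retain 197 |
|---|---|---|---|---|
| 0% | 200 | 121 | 81% | 197 |
| 5% | 190 | 115 | 79% | 208 |
| 10% | 180 | 109 | 76% | 219 |
| 15% | 170 | 103 | 74% | 232 |
| 20% | 160 | 97 | 71% | 247 |

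The last row in full: 200 × 0.80 = 160; 160 × 119/197 = 96.6; √(96.6/119) = 0.901; 2.80 × 0.901 − 1.96 = 0.56; Φ(0.56) ≈ 0.71; 197/0.80 = 246.25, so 247.

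**5. If lost patients contribute half their expected events.** At 20% loss, 200 × (1 − 0.10) × 119/197 = 108.7, about 109 events and 76% power.

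**The case against.** The strongest objection is that 160 patients and 97 events are a worst case. A reader might infer from the article that 200 included patients will leave 160 and 97. The documents do not support that, for three reasons.

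- The 20% is a ceiling, and it pools refusal with loss. Refusers are never among the 200. Reaching 160 needs no refusal and the maximum loss; if the whole 20% is refusal, there is no shortfall.
- The 97 events assume a fixed 60.4% event share and no events among lost patients before they are lost. Twelve months is a minimum, and the Abstract describes contact until RRT initiation or death, so follow-up may run longer and yield more events. Reaching 119 events among 160 patients would take 119/160 = 74%, which the text does not rule out.
- The power figures rest on assumptions about power, sidedness and test that the article does not state.

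All of this stands. It turns the size into a range and means that 160, 97 and 71% must not be presented as the expected result.

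Two readings would remove the point altogether. The first is that all of the 20% is refusal, but the allowance explicitly names loss of follow-up, and the Follow up section provides for withdrawal after consent. The second is that 197 already contains the allowance (157/0.80 = 196.25, so 197). Arithmetic alone cannot exclude this. It is unlikely, because 197 is paired with 119 events as what the calculation requires, and the 20% appears only in the following sentence, on recruitment. Nor can the 4.5–5 years conceal over-recruitment to 247, since the Abstract plans 200 over the same 5 years.

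**Conclusion.** The point holds as a range. The requirement, the allowance and the target are all stated, and the allowance is applied to recruitment time alone. The target of 200 absorbs 1.5% loss after inclusion, so the loss share of the 20% is not built into it.

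Depending on that unstated share, the cohort retains between 200 and as few as 160 patients. With the implied event share and no events from lost patients, events run from 121 down to 97, and power falls from about 80% to 71% at the extreme. A more moderate case, either 10% loss or 20% loss with half the expected events, gives about 109 events and 76%.

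The patient counts follow from the article's own figures. The event counts also need the 60.4% share to hold, and the power figures need the assumptions listed with the calculation. The article does not establish that the cohort will miss 119 events. It does establish that nothing in the stated target protects the cohort against the loss that the plan itself expects.

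**What to change.** In the Power analysis section, split the 20% into refusal before inclusion, which belongs in the recruitment time, and loss after inclusion, which belongs in the sample size. Then state the patients, events and power (or detectable effect) expected from 200 included patients after the loss share, as a range up to 20%, with the assumptions named. This replaces the present wording, which implies that 197 individuals or 119 events will be met. If 197 does already contain the allowance, say so and give the figure before inflation.

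Say also that patients lost to follow-up count for the time observed up to their last contact. The 4-monthly telephone contact makes this feasible, and it limits the power lost.

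The change is to wording only. No extra enrolment is needed. The one downside is a less favourable stated power.
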